### Statistical analysis

The analysis of primary endpoints, key secondary endpoints, and other secondary endpoints regarding short-term outcomes will begin as soon as 120 days after the patient enrolment period ends. Long-term outcome analysis of the secondary endpoint shall be performed upon completion of the 5-year follow-up period for all enrolled subjects.

Primary/key secondary endpoints: Summary statistics of patient background and surgical outcomes will be calculated, and the proportion of major complications and intraoperative vascular injury around the SMV and their causes will be summarised. Logistic regression analysis will be performed using the factors listed in the survey items that may influence the rate of major complications and intraoperative vascular injury around the SMV. A random-effects model will be used to account for the differences between institutions. Patients who underwent open conversion before the lymph node dissection will be excluded from the analysis of key secondary endpoints, and the relationship between the extent and location of the damaged vessel and the magnitude of the effect on the perioperative period will be considered.

Secondary endpoints: Summary statistics for patient background and other surgical outcomes will be calculated. A multivariate logistic regression or multiple regression analysis will be performed using the factors listed in the survey items that may influence outcomes. A random-effects model will be used to account for differences between the centres. The main endpoint for short-term outcomes for each subgroup is postoperative complications (Clavien–Dindo classification grade ≥ II), and group comparisons will be conducted after propensity score matching (differences between groups will be tested using Student’s t-test and the χ^2^ test) and logistic regression to identify confounders. Multiple regression analysis will be used to analyse continuous variables. A random-effects model will be used to account for the differences between institutions. The Kaplan–Meier method will be used to plot cumulative late complication curves, local and overall recurrence-free survival curves, and overall survival curves for long-term outcomes. To account for confounding factors, a multivariate Cox regression analysis will be performed using preoperative and postoperative factors that may contribute to recurrence and late complications, and risk factors will be examined. In addition to regression analysis of factors, each factor will be discussed from clinical and medical perspectives to reach a combined perspective.

The number of experienced cases will be added to the factors in the multivariate analysis to examine their effect on the outcome. The correlation of the number of cases experienced and outcomes (operation time and blood loss) with the learning curve will be evaluated using the moving average method and the cumulative sum curve.

Statistical significance will be set at *p* < 0.05.

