### Endpoints

The primary endpoint is the incidence of postoperative complications (Clavien–Dindo classification grade ≥ III) [35]. The rate of severe postoperative complications in all eligible patients will be investigated, and risk factors affecting them will be determined.

A key secondary endpoint is the incidence of intraoperative vascular injury around the SMV. The rate of intraoperative vascular injury around the surgical trunk in all eligible patients will be investigated, and risk factors affecting it will be extracted.

Other secondary endpoints include the incidence of postoperative complications (Clavien–Dindo classification grade ≥ II), 5-year overall survival, recurrence-free survival, and other short- and long-term outcomes (operative time, blood loss, conversion rate, degree of lymph node dissection, intraoperative complication rate, reoperation rate, R0 resection rate, local recurrence rate in the whole cohort and by stage, and incidence of bowel obstruction and herniated abdominal wall scarring). Factors influencing the above endpoints will be determined for all eligible patients. Furthermore, comparisons will be made between each subgroup, as shown in Table 1.

**Table 1 Tab1:** Secondary endpoints

1. Short-term results by approach (a. Medial approach vs. retroperitoneal approach; b. Medial approach vs. cranial approach; c. Retroperitoneal approach vs. cranial approach; a–c for laparoscopic surgery and robotic surgery, respectively)
2. Short-term results of robot-assisted and laparoscopic surgery (Comparison in all approaches, medial approach, retroperitoneal approach, and in each ASA-PS, respectively)
3. Short-term results by degree of lymph node dissection (D2, D3v, D3a)
4. Long-term results by approach, robot or laparoscopy, and degree of dissection
5. Impact of experience on short-term and long-term outcomes after the surgery performed by the surgeons before obtaining board certification in gastrointestinal surgery (including the investigation by each approach, robot/laparoscopy, and degree of lymph node dissection)
6. Impact of surgeons’ case volume prior to obtaining board certification in gastrointestinal surgery on short- and long-term outcomes following robot-assisted procedures
7. Impact of the participation of Endoscopic Surgical Skill Qualification-certified surgeons in surgery and their role in the procedure on short- and long-term outcomes
8. Impact of anastomosis method on short- and long-term outcomes

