Participating institution backgroundInstitution type and sizePatient backgroundPatient age; sex; body mass index; American Society of Anesthesiologists Physical Status; Eastern Cooperative Oncology Group performance status; albumin level; lymphocyte count; presence of dementia, diabetes, chronic kidney disease, chronic liver disease, or respiratory comorbidities; history of cardiac or cerebrovascular disease; use of steroids/immunomodulators and antithrombotic drugs; preoperative bowel obstruction; preoperative anaemia; abscess or peritonitis; preoperative therapy; history of laparotomy; timing of surgery; primary tumour location; and tumour stage at initial diagnosis (clinical stage, T factor, N factor).Technique and surgeonsWhether the surgeon is a board-certified gastrointestinal surgeon, whether an Endoscopic Surgical Skill Qualification-certified surgeon participates in the operation and his or her role, the approach, blood vessels to be dissected, procedure of dissecting the accessory right colic vein (via the cranial or caudal side), level and direction of lymph node dissection, instruments used during node dissection, method of anastomosis, combined resection of other organs, whether a robot is used, number of previous robotic-assisted right-sided colon resections (ileal resection, right hemicolectomy, or extended right hemicolectomy), and whether a robotic surgery proctor participates in the surgery if robotic surgery is used.Surgical outcomesThe date of surgery, operation time, blood loss, presence of intraoperative vascular injury, other intraoperative complications, 30-day postoperative survival, open conversion, intraoperative blood transfusion, details and grade of postoperative complications within 30 days (Clavien–Dindo classification grade ≥ II), onset and date of intervention for cases with anastomotic leakage/deep wound infection (surgical site infection [SSI]), enforcement and date of reoperation, drain placement, anti-adhesive placement, date of discharge, and operative death.In cases of intraoperative vascular injury:Timing of intraoperative vascular injury; response to intraoperative vascular injury; unplanned bowel resection due to bleeding; open conversion due to bleeding; final post-haemostatic status; and amount of blood transfusion, blood products, and albumin administered from intraoperative to postoperative day 3.Surgical deathsCause of death, date of death, and date of therapeutic intervention.Pathological and histological findings and postoperative courseTumour diameter, histological type (main), pathological stage, T-factor, N-factor, R-status, number of harvested lymph nodes, number of lymph node metastases, presence and details of adjuvant therapy, survival outcome, date of confirmation of final survival outcome, date of confirmation of recurrence, and type of initial recurrence.Patients with pStage 0 and pStage IV will be censored, and no follow-up will be performed after initial postoperative discharge. The development of intestinal obstruction (Clavien–Dindo classification grade ≥ II) and abdominal wall scar hernia will be investigated during follow-up. Patients will be followed up during the postoperative period according to the Japanese Society for Cancer of the Colon and Rectum guideline schedule, and tumour marker levels, thoracoabdominal computed tomography (CT) results, and colonoscopy results will be collected. Omitting observations as part of routine medical care will be deemed acceptable at the discretion of the treating physician [36].

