The definitions of these approaches were compiled using a previous survey on the details of each approach used in the attending institutions [see Additional file 1]. The description below covers the details of each approach used in the institutions that responded to the survey. Broadly speaking, the medial and cranial approaches are defined as procedures in which lymph node dissection precedes mesocolic mobilisation, whereas the retroperitoneal approach is defined as one in which mesocolic mobilisation precedes lymph node dissection.

Medial approach: dissection is initiated from the caudal side of the ileocecal artery, and lymph node dissection is performed prior to mesocolic mobilisation. The basic surgical procedure includes the following: (i) dissection of the ileocecal artery and vein from the retroperitoneum; (ii) lymph node dissection of the surgical trunk; (iii) dissection of the accessory right colonic vein; and (iv) mesocolic mobilisation by dissection of the cranial, caudal, and lateral attachments. This approach also includes cases in which cranial mobilisation, which creates a cranial termination point for lymph node dissection, is preceded by the standard procedure.

Retroperitoneal approach: mobilisation of the mesocolon from the retroperitoneum is initiated at its caudal origin, and lymph node dissection is performed after mesocolic mobilisation. The basic surgical procedure includes the following: (i) mobilisation of the mesocolon from the retroperitoneum initiated at its caudal origin (regardless of the degree of lateral mobilisation); (ii) lymph node dissection of the surgical trunk; and (iii) dissection of the accessory right colonic vein, opening of the omental bursa, or hepatic mobilisation. This approach also includes cases in which cranial mobilisation, which creates a cranial termination point for lymph node dissection, is preceded by standard lymph node dissection.

Cranial approach: dissection begins by opening the omental bursa and hepatic attachment, and lymph node dissection is performed prior to mesocolic mobilisation. The basic surgical procedure includes the following: (i) opening of the omental bursa, (ii) dissection of the right accessory colic vein or hepatic attachment, (iii) lymph node dissection along the surgical trunk, and (iv) mobilisation of the lateral/caudal attachments. Whether lymph node dissection is performed from the cranial to the caudal side or from the caudal to the cranial side does not matter.

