(15) Robot usage: classified into da Vinci (except SP), Hinotori, Hugo, other models, or no usage.(16) Anastomosis method: classified into functional end-to-end anastomosis, overlapping anastomosis, delta anastomosis, and others. Additionally classified as intracorporeal or via a small laparotomy.(17) Methods for dissecting the right accessory colonic vein: dissection from the cranial and caudal sides.(18) Direction of lymph node dissection: the dissection procedure of the surgical trunk is classified into caudal to cranial, cranial to caudal, and caudal to cranial after setting a cranial termination point.(19) Lymph node dissection: classified as D0–1, D2, D3v, and D3a. The definitions are as follows.aFor the ileocecal and right colic arteryD2, the ileocecal or right colic artery is dissected proximally without SMV exposure; D3v, the anterior face of the SMV is exposed, and the ileocecal or right colic artery is dissected proximally; D3a, the anterior face of the SMA is additionally exposed, and the ileocecal or right colic artery is dissected at the root.bFor the middle colic arteryD2, the right/left branch of the middle colic artery (MCA) is dissected proximally. The main trunk of the MCA is not exposed; D3v, the main trunk of the MCA and anterior face of the SMV are exposed, and the right branch or trunk of the MCA is dissected proximally; D3a, the MCA main trunk and anterior face of the SMA are exposed, and the right branch or trunk of the MCA is dissected at the root.

The degree of dissection is judged based on the dissection of the dominant main vessel, regardless of SMV exposure during the procedure.

(20) Synchronous other-organ resection: description of synchronously resected organs: duodenum, jejunoileum, colon, liver, gallbladder, pancreas, iliopsoas muscle, inferior vena cava, aorta, iliac artery and vein, SMA and SMV, peritoneum of the abdominal wall adjacent to the colon, gonadal vessels, mesentery of other intestinal tracts, and others.(21) Devices used during lymph node dissection: monopolar, bipolar (including sealing devices), ultrasonic coagulation, and incision devices.(22) Intraoperative vascular injury: intraoperative injury to any of the following vascular organs: SMA, SMV, accessory right colonic vein, ileocecal artery, right colonic artery, MCA, anterior superior pancreaticoduodenal vein, right gastroduodenal vein, gastrocolic trunk, terminal ileal branch, first jejunal vein, and others (e.g., inferior vena cava).

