(23) Final bleeding control: possible/impossible (operative death).(24) Timing of intraoperative vascular injury: during lymph node dissection, mobilisation, intracorporeal anastomosis, extracorporeal anastomosis, and others (described at the time of adhesion dissection, drain insertion, etc.).(25) Other intraoperative complications: list those requiring intraoperative intervention (e.g., injury to other organs).(26) Open conversion: a skin incision ≥ 8 cm is generally defined as an open conversion. However, if the incision exceeds 8 cm solely for the purpose of tumor extraction, it shall not be considered an open conversion.(27) Postoperative complications (within 30 days): Clavien–Dindo classification grade ≥ II should be used.(28) Date of onset of anastomotic leakage/deep SSI: the date of onset is defined as the earliest time of abnormality during the initial physical examination, such as fever, abdominal pain, abnormal discharge from the drainage tube, blood test, and imaging.(29) Treatment intervention date: the date of treatment intervention is defined as the date corresponding to any of the following: administration of medical therapy (in the case of Clavien–Dindo classification grade II); performance of endoscopic, surgical, or interventional radiology (IVR) procedures without general anesthesia (grade IIIa); performance of endoscopic, surgical, or IVR procedures with general anesthesia (grade IIIb); or admission to the intensive care unit (ICU) (grade IV). Additionally, in cases of anastomotic leakage or deep surgical site infection (SSI), the date should be recorded if a new percutaneous drain is inserted or an existing one is replaced.(30) 30-day death: death from any cause within 30 days of surgery.(31) Surgical death: 30-day death or death during hospitalisation 31–90 days postoperatively.(32) Histological type, pathological stage, T and N stages, and R status: according to the Japanese Classification of Colorectal, Appendiceal, and Anal Carcinoma, third English Edition [37].(33) Postoperative adjuvant therapy: indicate whether at least one course has been completed, and specify the type of chemotherapy administered.(34) Recurrence-free survival: duration from the date of first treatment (surgery or start of preoperative therapy) to the date of the last confirmed recurrence-free/recurrence.(35) Local recurrence: local recurrence will be assessed based solely on the initial recurrence, with distinctions made between lymph node recurrence, anastomotic site recurrence, and other locations.(36) Intestinal obstruction during follow-up (Clavien–Dindo classification grade ≥ II): only the first occurrence 30 days after surgery will be considered.(37) Abdominal wall scar hernia: this will be diagnosed based on imaging findings, such as CT, or palpation of the hernia in the surgical scar. Only the first occurrence 30 days after surgery will be considered.

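### The key secondary analysis drops patients converted to open surgery before lymph node dissection, although a vascular injury can itself cause that conversion

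*Protocol article*

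**What the plan says.** The protocol article describes the analysis set for the key secondary endpoint in two places.

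- Endpoints: "The rate of intraoperative vascular injury around the surgical trunk in all eligible patients will be investigated".
- Statistical analysis, paragraph on primary and key secondary endpoints: "Patients who underwent open conversion before the lymph node dissection will be excluded from the analysis of key secondary endpoints". The reason for conversion plays no part in this rule.

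Four other statements bear on what the rule removes.

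- Definition of assessment data, item 24, does not confine injuries to node dissection: "Timing of intraoperative vascular injury: during lymph node dissection, mobilisation, intracorporeal anastomosis, extracorporeal anastomosis, and others". Adhesion dissection is given as an example of the last category.
- Item 22 counts "intraoperative injury to any of the following vascular organs: SMA, SMV, accessory right colonic vein, ileocecal artery" and further vessels, some of which are handled before node dissection in some approaches.
- Observation, investigation data, and methods lists, for injured cases, "unplanned bowel resection due to bleeding; open conversion due to bleeding".
- Item 14 separates the approaches largely by what comes before node dissection. For one of them, "the retroperitoneal approach is defined as one in which mesocolic mobilisation precedes lymph node dissection".

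The planned analysis of this endpoint is a logistic regression on survey items with random effects for institution. Approach is one of the survey items.

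**The concern.** The two statements of the analysis set cannot both be followed. If the exclusion is applied as written, membership of the analysis set depends on an intraoperative event that the outcome can cause. A patient whose vessel is injured during mobilisation, and who is converted because of the bleeding, had the event and is then treated as if never observed.

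Two things are at stake. The first is the reported incidence of vascular injury, which the Discussion presents as something this study will establish. The lost cases are those in which an injury came with an early conversion, so they are plausibly among the more serious, although the protocol has no data on that. The second is approach as a risk factor for injury. If the phase before node dissection is longer in one approach than another, injured patients have more opportunity to drop out of one group.

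**Working it through.** **Plan's own figures.** The protocol gives no number for early conversions or for injuries removed by the rule. Its one sample size figure, about 2,000, concerns the primary endpoint: 1.96² × 0.05 × 0.95 / 0.01² = 1,825 by the normal approximation, and about 1,930 with exact binomial limits. At 2,000 the half-width is 0.96 points (0.98 exact). That figure stands and does not bear on this point.

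**Order of steps (item 14).**

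| Approach | Before trunk node dissection | After it |
|---|---|---|
| Medial | Freeing the ileocecal artery and vein; in some cases cranial mobilisation | Accessory right colic vein; mesocolic mobilisation |
| Retroperitoneal | Mesocolic mobilisation from the caudal side | Accessory right colic vein, omental bursa or hepatic mobilisation |
| Cranial | Opening the omental bursa; accessory vein or hepatic attachment | Lateral and caudal mobilisation |

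For the cranial approach the text reads "ii) dissection of the right accessory colic vein or hepatic attachment, (iii) lymph node dissection along the surgical trunk", so the vein comes first in some cases, not necessarily all. The window for an excluded injury is therefore longest on paper for the retroperitoneal approach. It is longer for the cranial approach where the vein is taken first, and shorter but not zero for the medial approach.

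**Inputs for an illustration.**

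- p = 0.03, the background figure for D3 dissections (Background); N = 2,000 (Target number of cases).
- s = share of an approach's injuries that occur before node dissection: not given, assumed 5–30%.
- c = share of those that lead to conversion before node dissection: not given, assumed 10–50%.

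**Expected events.** 0.03 × 2,000 = 60 injuries. The 95% half-width is 1.96 × √(0.03 × 0.97 / 2,000) = 0.75 points.

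**Loss in one approach, per 1,000 patients.** Expected injuries are 30, and those removed are 30 × s × c.

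- Low: 30 × 0.05 × 0.10 = 0.15.
- High: 30 × 0.30 × 0.50 = 4.5.

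**Apparent odds ratio with no true difference and no loss in the comparator.** Write L = p·s·c. The apparent rate is r = (p − L)/(1 − L), so its odds are (p − L)/(1 − p). Dividing by p/(1 − p) gives an odds ratio of 1 − s·c.

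- Low: 1 − 0.005 = 0.995.
- High: 1 − 0.15 = 0.85.

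If the comparator also loses a share m, the ratio is (1 − s·c)/(1 − m). With m = 5% the high case becomes 0.85/0.95 = 0.89.

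**Against sampling error.** In the high case the groups are 25.5/995.5 and 30/1,000. SE(log OR) = √(1/25.5 + 1/970 + 1/30 + 1/970) = 0.273. The 95% interval is 0.85 × exp(±1.96 × 0.273), about 0.50 to 1.45. The chance of a two-sided p < 0.05 is about 9%.

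**Overall rate.** If half the cohort has the high loss and the rest none, (60 − 4.5)/(2,000 − 4.5) = 2.78% instead of 3.00%.

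**Injury-free early conversions.** The rule removes these too, which pushes the rate up slightly. With 10 early conversions per 1,000 (assumed), none of them injured, the rate becomes 30/990 = 3.03%. With 4.5 injured it is 25.5/990 = 2.58%. The net effect is downward once injuries are more frequent among early conversions than in the cohort (above 3%). That is likely if bleeding is among the reasons for converting.

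**The case against.** The best defence is that a patient converted before node dissection never underwent the endoscopic dissection under study. The 3% background figure refers to D3 dissections, and the Discussion ties vascular injury to that step. This stands for early conversions without injury, for example because of adhesions. It does not justify deleting a patient who already had the event, and the rule makes no such distinction. It also limits the remedy: counting every injury up to closure would attribute injuries during open dissection to an endoscopic approach.

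A reader might infer that the comparisons of approaches in Table 1 are biased as a whole. The protocol does not support that. The exclusion is stated only for the key secondary endpoint, and the Statistical analysis section makes Clavien–Dindo grade ≥ II complications the main short-term endpoint of the subgroup comparisons, with no such exclusion.

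A reader might also infer that only the non-medial approaches can lose injured patients. The medial approach begins with work on the ileocecal vessels, and the ileocecal artery is a listed injury vessel; cranial mobilisation may also come first. Nor is the cranial approach one that mobilises the mesocolon first. A loss of zero in the medial group is an assumption of the illustration.

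Finally, the effect may be small. Within the assumed range it lies inside sampling error. Much larger distortions would need more injured early conversions than the protocol gives reason to expect: losing half of 30 injuries requires at least 15 early conversions per 1,000, all with an injury.

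**Conclusion.** The point holds in a limited form. The analysis set for the key secondary endpoint is stated in two incompatible ways, and the restrictive version lets the outcome trigger exclusion. Followed as written, it deletes true events and probably understates the injury rate, by an amount that cannot be computed from the protocol.

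Under the assumed shares, 0.5–15% of an approach's injuries are lost, and the spurious odds ratio lies between 0.995 and 0.85 if the comparator loses none. That the window for loss differs by approach follows from the protocol's definitions. How many injuries fall in it does not, so bias in approach as a risk factor is possible but not shown. The primary endpoint, the sample size and the main subgroup endpoint are untouched.

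**What to change.** Reconcile the two sections in the direction of Endpoints.

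- Report the injury rate in all eligible patients. For those converted before node dissection, count as an event any vascular injury meeting the endpoint definition that occurs before or at conversion. Report injuries that first arise in open dissection after such a conversion separately.
- If an exclusion is wanted for patients not exposed to endoscopic node dissection, limit it to conversions before node dissection without prior vascular injury or bleeding, and present it as a sensitivity analysis.
- Report the number of early conversions by approach and reason, so that readers can see how much the choice of set matters.

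The cost is a sentence or two of text and a little more analysis work; no extra patients are needed. Timing of injury and conversion due to bleeding are already collected, and the present rule already requires knowing whether conversion came before node dissection. The article lists no other reasons for conversion, so the split may be bleeding versus other. The reported rate may come out slightly higher.

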**Fig. 1 Fig1:**
[figure not shown]
Questionnaire regarding the preferred approach for conventional laparoscopic right colectomy**.** A nationwide questionnaire was conducted in 2023 by the Japan Society of Laparoscopic Colorectal Surgery. The most preferred approach in each institution is shown. According to the survey, the medial and retroperitoneal approaches are the most preferred

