**Fig. 3 Fig3:**
[figure not shown]
Questionnaire regarding the preferred anastomosis for laparoscopic right colectomy. A nationwide questionnaire conducted in 2023 by the Japan Society of Laparoscopic Colorectal Surgery revealed institutional preferences for anastomosis techniques. (**a**) Extracorporeal anastomosis was predominant in conventional laparoscopic surgery, (**b**) while intracorporeal anastomosis was favoured in robot-assisted procedures

Given the above background, we have designed this prospective observational study to investigate factors influencing the safety of laparoscopic right-sided colon resection.

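### The tests named for propensity-matched comparisons ignore institution, and the planned random-effects model is not tied to them; for centre-driven exposures such as surgical approach, the type I error can exceed 5%

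*Protocol article*

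**What the plan says.** The secondary-endpoint paragraph of the Statistical analysis section covers the comparisons listed in Table 1 (Endpoints section). It sets the outcome: "The main endpoint for short-term outcomes for each subgroup is postoperative complications" of Clavien–Dindo grade II or higher. It then names the method: "group comparisons will be conducted after propensity score matching (differences between groups will be tested using Student’s t-test" and the χ² test), followed by "and logistic regression to identify confounders". Continuous outcomes get multiple regression. The next sentence reads "A random-effects model will be used to account for the differences between institutions". The level is fixed for all analyses: "Statistical significance will be set at" p < 0.05.

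Table 1, item 1, lists the approach comparisons: "Medial approach vs. retroperitoneal approach; b. Medial approach vs. cranial approach; c. Retroperitoneal approach vs. cranial approach", each to be done separately for laparoscopic and for robotic surgery. Later items compare robot with laparoscopy, extent of dissection and anastomosis method.

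On how technique is distributed over hospitals, the legend of Fig. 1 says "The most preferred approach in each institution is shown", and Fig. 2 does the same for robotic surgery. The legend of Fig. 3 says that the survey "revealed institutional preferences for anastomosis techniques".

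**The concern.** Student's t-test and the χ² test compute their standard errors as if every patient were an independent observation, and neither has a place for an institution effect. They are the only methods that the paragraph names for testing differences between matched groups. The logistic regression in the same sentence is given another purpose, finding confounders. The random-effects sentence stands apart, and nothing says that it governs the matched comparisons or which result counts if the two disagree.

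This matters most when the exposure varies between hospitals rather than within them. Differences in outcome between hospitals then feed directly into the contrast between techniques, and the unclustered test takes them for evidence about the technique. The Background names the safest approach, the platform and the anastomosis as unresolved questions that the data collection was built to address. A finding that one technique is safer could partly reflect chance differences between the hospitals that happen to use it, at a rate above the stated 5%.

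**Working it through.** **Inputs from the protocol article.** 2,000 patients and 73 facilities (Abstract); nominal level 0.05, taken as two-sided because the side is not stated; approach comparisons split by platform (Table 1, item 1); nearly equal numbers of laparoscopic and robotic procedures expected (Discussion), so about 1,000 patients per platform.

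**Assumptions, none given in the article.** Outcome ICC between institutions of 0.01, 0.02 or 0.05; patients of each platform spread over all 73 centres; matching keeps either all 1,000 or 600 of them; centre sizes equal or with a coefficient of variation (CV) of 0.6.

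**Formula, for an exposure fixed by centre.** With mean centre size m, the design effect is DE = 1 + (m − 1) × ICC. With unequal centres it is DE = 1 + [(1 + CV²) × m − 1] × ICC. The actual level of the unclustered test is α = 2 × [1 − Φ(1.96/√DE)].

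**Reference point.** The article states no error rate for these comparisons beyond p < 0.05. At ICC = 0, DE = 1 and the formula returns 5.0%.

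**Within-platform approach comparison, no loss to matching.** m = 1,000/73 = 13.7. At ICC 0.02 with equal centres, DE = 1 + 12.7 × 0.02 = 1.254, √DE = 1.120, 1.96/1.120 = 1.750, so α = 8.0%.

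**The same with 600 patients kept.** m = 600/73 = 8.22. At ICC 0.02, DE = 1 + 7.22 × 0.02 = 1.144, √DE = 1.070, 1.96/1.070 = 1.832, so α = 6.7%.

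| Patients in comparison | Centre sizes | ICC 0.01 | ICC 0.02 | ICC 0.05 |
|---|---|---|---|---|
| 1,000 | equal | 6.5% | 8.0% | 12.5% |
| 1,000 | CV 0.6 | 7.1% | 9.2% | 15.3% |
| 600 | equal | 5.8% | 6.7% | 9.3% |
| 600 | CV 0.6 | 6.2% | 7.4% | 11.1% |

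**How far this depends on exposure being centre-driven.** A simulation under no true effect used all 2,000 patients, 73 centres, CV 0.6, a 10% event rate (assumed) and 6,000 runs per cell. It gave these rejection rates for the unclustered χ² test:

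| Exposure | ICC 0.01 | ICC 0.02 | ICC 0.05 |
|---|---|---|---|
| Fixed by centre | 9.8% | 13.9% | 24.5% |
| Partly by centre (exposure ICC 0.5) | 7.0% | 9.2% | 15.5% |
| Weakly by centre (exposure ICC 0.2) | 5.8% | 6.9% | 9.4% |
| Balanced within every centre | 5.6% | 4.8% | 4.7% |

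The first row agrees with the formula at full volume and CV 0.6 (9.3%, 13.6%, 24.3%). The last row shows no inflation. The second table shows the pattern and not the size for the approach comparisons, which do not use all 2,000 patients. Neither calculation includes the matching step itself; the 600-patient rows only imitate its loss of patients. If one platform's cases come from fewer than 73 centres, m and the inflation are larger than shown.

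**The case against.** The strongest reply is that the paragraph already deals with institutions. It plans regressions beside the matched tests and a random-effects model for institutional differences, so the t and χ² results may be meant as the simple contrast and the mixed model as the adjusted result. That is a possible reading, and it shows that the authors want clustering handled. But the text does not say it, and the methods it attaches to testing matched differences are the unclustered ones. This is a named method rather than a detail left to a fuller document.

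A second reply is that centre-driven exposure is not established. Much of this stands:
- For approach, Figs. 1 and 2 give each institution's favourite, not the share of its patients treated that way.
- For anastomosis, Fig. 3 shows that the preferred technique differs between laparoscopic and robotic surgery, so it can vary within a hospital.
- For robot use, the only institution-level statement is the entry condition of at least 10 prior cases (Selection criteria). The Discussion describes sites proficient in both platforms.

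A reader might infer that all these comparisons have false-positive rates well above 5%, up to the 24.5% in the simulation. The article does not support that. The figure needs all 2,000 patients, exposure wholly fixed by centre and an ICC of 0.05, whereas the approach comparisons are split by platform and matching reduces the centres' contributions further.

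A reader might also infer that matching uses patient factors only and crosses institutions. The article does not give the propensity variables or say whether matching is within centre, and it may leave both to the full protocol. Pairwise matched sets with different populations are a known property of that design, and a multi-group weighting scheme would be a preference.

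**Conclusion.** The point holds in a limited and conditional form. The tests named for the matched comparisons ignore institution, and the planned random-effects model is not connected to them. For exposures that follow institutional preference, the actual level can exceed 5%. For within-platform approach comparisons with exposure fixed by centre, the excess is modest at ICCs of 0.01–0.02 (about 6–8%, reaching 9% with unequal centres and no loss to matching). It is clearer at 0.05 (about 9–15%). These sizes rest on assumed ICCs, centre-size variation and matching yield, and on the extreme of one approach per centre; partial preference gives less, and balance within centres gives none.

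The support is best for approach, weaker for anastomosis and absent for robot use. Only secondary comparisons are affected: the regressions for the primary and key secondary endpoints are given an institution random effect in their own paragraph.

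**What to change.** State in the secondary-endpoint paragraph that each propensity-matched comparison is decided by a regression on the matched sample, with either an institution random effect or institution-clustered (robust) standard errors. State that the t and χ² results are descriptive only. This ties the random-effects model that the article already plans to the comparisons that need it, and settles which result counts if the two differ.

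The cost is a change of wording and a little more programming. Intervals will be somewhat wider where technique follows the centre. No new data are required, since institution is known for every patient.
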